### Study Objectives and Hypothesis

The COVID-19 pandemic has undoubtedly imposed a wide range of restrictions on older adults' participation in social activities, increasing their level of loneliness. Low-income older adults who live alone and have limited access to the Internet are at higher risk of loneliness (52,53). Our primary aim is to evaluate whether a Tele-Behavioral Activation (Tele-BA) and a Tele-Mindfulness (Tele-MF) intervention are more effective than the active control consisting of Tele-Befriending (Tele-BF) in reducing loneliness (i.e., one of the primary outcomes, see below for details on all measures) among community-dwelling older Chinese adults in Hong Kong who live alone and in poverty and have limited access to the Internet. Tele-BA focuses on increasing and reinforcing a target individual's engagement in meaningful life activities (31), Tele-MF focuses on increasing awareness of the present moment with acceptance (20), whereas Tele-BF refers to a volunteer's provision of emotional support for the target individual who reports loneliness (50). We hypothesize that Tele-BA and Tele-MF interventions are effective in reducing perceived loneliness, measured at the 4-week, 3-month, 6-month, and 12-month follow-up assessments, compared to Tele-BF group.

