#### Planned Analysis of the Effects of the Intervention

The effects of the intervention on loneliness are assessed using mixed models for repeated measures. Specifically, a conditional growth model analysis with an unstructured covariance matrix is conducted using a Group (two intervention groups and one control group)  $\times$  Time (baseline, 4 weeks, and 3-, 6-, and 12-month follow-ups) interaction as an indicator of the intervention effects. For sensitivity analysis, a similar mixed model for repeated measures with an unstructured covariance matrix, but with the ANOVA model, is used. The demographic characteristics that show significant differences across groups at baseline are controlled for in the models. In addition, an “intention-to-treat” analysis is used to assess differences in outcomes by incorporating participants who do not complete the study. The intention-to-treat principle is also applied, and all statistical analyses are conducted using SPSS 28. In order to test the effect of the proposed mediators, path analyses with manifest variables will be run with indirect effect specified and tested with 95% bias-corrected confidence intervals resulting from 1000 bootstraps in Mplus 8. Mindfulness, happy/meaningful events, CRP, the position of candidate genes, polygenic risk scores and SNPs are potential mediators to be tested.

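### The indicator of effect is the interaction of a three-level Group factor with Time and is not tied to the two comparisons with befriending that the hypothesis states; read as a joint test, it has no direction

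*Protocol*

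**What the plan says.** Study Objectives and Hypothesis gives the aim as whether the two interventions "are more effective than the active control consisting of Tele-Befriending (Tele-BF) in reducing loneliness". The hypothesis has a direction and a named comparator: "We hypothesize that Tele-BA and Tele-MF interventions are effective in reducing perceived loneliness, measured at the 4-week, 3-month, 6-month, and 12-month follow-up assessments, compared to" the Tele-BF group. That makes two claims, BA against BF and MF against BF.

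Planned Analysis of the Effects of the Intervention describes the model: "a conditional growth model analysis with an unstructured covariance matrix is conducted using a Group" by Time interaction. The Group factor has three levels ("Group (two intervention groups and one control group") and Time has five ("Time (baseline, 4 weeks, and 3-, 6-, and 12-month follow-ups"). This term is taken as the "interaction as an indicator of the intervention effects". The sensitivity analysis keeps the same structure in ANOVA form. The section names no reference arm, no contrast against Tele-BF and no direction.

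**The concern.** The point is not that detail has been left to a statistical analysis plan. The protocol does name what will indicate an effect, and the natural reading of what it names, the interaction of a three-level factor with Time, is a joint test. That test asks whether any of the three arms differ in their course over time. It responds equally to benefit and to harm, and it also responds to a difference between BA and MF that says nothing about befriending.

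Two wrong conclusions become possible. A significant interaction could be reported as an intervention effect when one arm does worse than befriending, or when the two interventions lie on either side of it without either being shown better. Conversely, an arm could beat befriending on its own contrast while the joint term is not significant. A plan written to this text could inherit the gap between hypothesis and test.

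**Working it through.** **Inputs.** From the protocol: three groups, five time points, 289 evaluable per group, effect size 0.25, alpha 0.05, power 90%, dropout 10%. Assumed here because the protocol does not give them: SD 1, two-sided tests, compound symmetry with within-person correlation 0.3, 0.5 or 0.7, and the true effects in each scenario.

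**1. The plan's own figure.** For two means, n = 2(z₁₋α/₂ + z_power)²/d².
- 90% power: 2(1.960 + 1.282)²/0.0625 ≈ 336, or 337 with the t correction.
- 85% power: 2(1.960 + 1.036)²/0.0625 ≈ 287; the t-based value is 288.3, which rounds up to 289.

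So 289 does not reproduce as a two-sided pairwise size at the stated 90%. The dropout step does reproduce: 289/0.9 = 321.1, rounded up to 322, and 3 × 322 = 966. I use 289 per arm below only as the planned evaluable number.

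**2. Degrees of freedom.** Categorical time: (3−1)(5−1) = 8. Linear slope: (3−1) × 1 = 2. Neither statistic carries a sign.

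**3. Simplified scale: three means at one time, 289 per arm.** The joint F test has non-centrality λ = n Σ(μᵢ − μ̄)². Contrasts against BF are two-sided at 0.05, unadjusted.

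| Scenario (in SD) | λ | Joint test significant | Joint test significant, neither arm significantly better than BF |
|---|---|---|---|
| (a) BA = BF, MF 0.25 worse | 289 × 0.04167 = 12.04 | 88% | 86% |
| (b) BA 0.125 better, MF 0.125 worse | 289 × 0.03125 = 9.03 | 77% | 46% |

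In (b), power to show BA better than BF is 32%. In (c), with BA 0.20 and MF 0.10 better, 14% of trials have an arm significantly better than BF while the joint test is not significant. At 0.025 per contrast this falls to 4.3%. The simulation used 400,000 draws.

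**4. The interaction itself.** For a linear slope with times 0, 1, 3, 6 and 12 months, Σ(t − t̄)² = 93.2. If one arm departs linearly from the other two by 0.25 SD at 12 months, λ = n(2/3)(0.25/12)² × 93.2/(1 − ρ). At ρ = 0.5, λ = 289 × 0.6667 × 0.000434 × 93.2/0.5 = 15.59. Power is 0.95 at 2 df and 0.82 at 8 df. The same values arise when MF alone is worse, when both interventions are worse, and when BA alone is better.

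Over ρ = 0.3 to 0.7, with the 0.25 SD departure either constant from the first follow-up or growing linearly, the probability of significance is 0.65 to 0.99 at 8 df and 0.38 to 0.997 at 2 df.

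With BA 0.125 better and MF 0.125 worse at 12 months (linear, ρ = 0.5), the interaction is significant in 67% of runs at 8 df and 88% at 2 df. In 52% and 55% of those significant runs, no contrast against BF is significantly favourable, even unadjusted.

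**5. Two named contrasts.** At d = 0.25 and 289 per arm, d√(n/2) = 3.005. Power is Φ(3.005 − 1.960) = 85.2% at two-sided 0.05 and Φ(3.005 − 2.241) = 77.8% at 0.025. With no true difference anywhere, the chance that at least one contrast is significant is about 9% at 0.05 each and about 4.7% at 0.025 each.

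**The case against.** The protocol never uses the word omnibus, states no degrees of freedom, and gives no rule that a significant interaction makes an intervention effective. It identifies one arm as control. With that arm as the reference level, the same growth model yields two signed Group by Time coefficients, BA against BF and MF against BF, which are what the hypothesis needs. The comparator and direction are stated in the objectives, and an unseen analysis plan may name the contrasts. Harm would be mistaken for benefit only by someone who ignored the estimates.

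Most of this stands. A reader might infer that the planned model does not test the hypothesis at all. The text does not support that: the model is adequate, and what is loose is the term named as the indicator. A reader might also infer that the sample size section is a pairwise calculation that conflicts with a joint test. The section gives one effect size and a number per group, but never says pairwise, and 289 does not reproduce as a two-sided pairwise size at 90% power, so that remains only an inference.

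The objection also limits the numbers. The 88% belongs to a single-time comparison of three means, not to the planned repeated-measures term. Scenarios (a) and (b) suppose mindfulness to be worse than befriending, which the protocol does not anticipate. The 14% in (c) depends on unadjusted contrasts.

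The objection does not remove the mismatch. The analysis section does name an indicator, and nothing there ties it to the two comparisons.

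**Conclusion.** The concern holds as a mismatch between the stated hypothesis and the stated indicator. Two directional comparisons with Tele-BF are hypothesised, while the named indicator, read as a joint test, is undirected and counts harm and BA-MF differences as readily as benefit. That property follows from the structure of the test and needs no assumption about effect size or correlation.

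The size does rest on assumptions. It is about 88% in scenario (a) on the simplified scale; on the interaction itself the wide ranges in step 4 apply, because the protocol gives neither the correlation nor the shape of effect over time. The data and model suffice for the right comparisons, so this should be corrected in the wording of the analysis section and does not call for a redesign.

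**What to change.** In Planned Analysis of the Effects of the Intervention:

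- Set Tele-BF as the reference group and name two Group by Time contrasts from the same model as the indicators of effect: Tele-BA versus Tele-BF and Tele-MF versus Tele-BF.
- State whether each contrast is a difference in slope or a difference in change from baseline at a named visit. With categorical time there are eight contrasts against BF (two interventions by four follow-ups), so this choice must be made.
- Report each contrast with its estimate, confidence interval and direction, and call an intervention effective only on its own favourable contrast.
- Control the error rate over the two contrasts, for example by Holm, or by keeping a joint test as a gate before them. If a gate is used, it should be the 2-df joint test of these same two contrasts, because an 8-df test could pass on differences at other visits.

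The contrasts need no new data and no new model. The cost is some power per contrast if alpha is split: about 78% instead of 85% at 0.25 SD with 289 per arm under an equal split, which is the worst case for Holm. A gate avoids the split but gives up trials such as those in scenario (c), where an arm beats befriending and the joint test is not significant. Leaving the two contrasts unadjusted is not a neutral alternative, since it allows about a 9% chance of at least one false positive.

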## Supplement 1. Study Protocol

### Sample Size

A required sample size for the RCT on loneliness was estimated for one of the primary outcomes, that is, loneliness assessed by UCLA Loneliness Scale (54). A previous intervention study on reducing loneliness in older adults yielded an effect size of 0.5 (31). To be more conservative, we estimate the sample size based on a smaller effect size, i.e., 0.25. To detect an effect size of 0.25 at an alpha error rate of 0.05 and a power of 90%, the estimated sample size is 289 participants in each group. With an anticipated drop-out rate of 10% over a period of 6 months, the necessary sample size is 322 participants per group at baseline ( $N=966$  in total).

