### Randomization

After completing baseline assessment, participants are randomly assigned to either Tele-BA, Tele-MF, or Tele-BF using an online random number generated by a research assistant. Participants are then informed of their assigned intervention, and Tele-BA participants receive copies of BA worksheets. Due to the nature of the intervention, participants cannot be blinded as the types of activities in each intervention group are distinct.

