### Demographic Information

In addition, the following sociodemographic information is collected as potential covariates: (1) age; (2) gender; (3) marital status; (4) number of children; (5) education level; (6) employment status; (7) household income.

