### Planned Statistical Analysis of the Effects of the Intervention

#### Planned Preliminary Analysis

Descriptive statistics, correlation analysis, and attrition analysis (t-tests to compare the covariates and outcome variables of participants who drop out and those who complete the intervention) and randomization tests (one-way analysis of variance [ANOVA]) are conducted to test for differences in covariates and outcome variables between conditions using SPSS 28.

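### Demographic covariates are chosen by baseline significance tests, which select on chance imbalance and leave the covariate set open; the usable precision lies in baseline loneliness

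*Protocol*

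**What the plan says.** Three sections of the protocol together make up the rule.

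- Demographic Information: "the following sociodemographic information is collected as potential covariates". Seven variables follow (age, gender, marital status, number of children, education, employment, household income), and none is fixed as a covariate.
- Planned Preliminary Analysis: "randomization tests (one-way analysis of variance [ANOVA]) are conducted to test for differences in covariates and outcome variables between conditions". No test level is given.
- Planned Analysis of the Effects of the Intervention: "The demographic characteristics that show significant differences across groups at baseline are controlled for in the models".

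Allocation is random: "participants are randomly assigned to either Tele-BA, Tele-MF, or Tele-BF using an online random number generated by a research assistant". The section names no stratification factor.

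The primary model is described thus: "a conditional growth model analysis with an unstructured covariance matrix is conducted using a Group (two intervention groups and one control group", crossed with Time, with the "interaction as an indicator of the intervention effects". Baseline is listed as one of the Time levels. Baseline loneliness is therefore part of the outcome vector and not a covariate.

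**The concern.** If randomisation was carried out properly, every baseline difference between arms is chance, and a p-value for it carries no information about which variables predict loneliness. The rule can leave out a strong predictor that happens to be balanced and bring in an irrelevant variable that happens not to be. It also means that the covariate list of the primary model is known only after allocation and baseline data have been put together. The selection step itself is loosely defined: the level is not stated, and one-way ANOVA does not suit nominal variables such as marital or employment status.

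This is a rule that the protocol states, not a detail left to an unseen analysis plan. At stake are a covariate set fixed in advance and the precision that a fixed, prognostic set could bring.

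**Working it through.** **Inputs.** From the protocol: seven candidate demographics; three arms; "the estimated sample size is 289 participants in each group" before dropout; standardised effect 0.25; alpha 0.05; baseline as a Time level. Assumed, because the protocol does not give them: a 5% level for the baseline tests, two-sided testing, the joint R² of the demographics with loneliness, and the baseline to follow-up correlation rho.

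**Step 1. Starting power.** The protocol attaches no figure to the covariate rule, so the sample size is the reference. SE = √(2/289) = 0.0832 SD; 0.25/0.0832 = 3.005; power = Φ(3.005 − 1.960) = 85.2%. The stated 90% is not reproduced: two-sided testing would need 337 per arm, and one-sided 275. That is a separate matter; here 85.2% serves only as the base for comparison.

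**Step 2. How often the rule is triggered.** With independent tests, P(at least one of seven) = 1 − 0.95⁷ = 30.2%; simulation gave 28% to 31%. If the seven tests were fully dependent, the figure would be 5%. Correlated demographics lie in between. Up to 2⁷ = 128 covariate sets are possible.

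**Step 3. Type I error.** Simulation: three arms of 289, seven independent covariates, ANOVA selection at p < 0.05, rho = 0.5, 3,000 null runs for each R². Rejection rates under the rule were 4.2% to 5.0% for a single follow-up contrast and 5.2% to 5.4% for change from baseline. There is no inflation.

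**Step 4. Effect on the stated model.** Write a time-constant demographic X with main effect γ. It adds γX to every visit, so (Y_visit + γX) − (Y_baseline + γX) is free of X. The Group by Time contrast is a contrast of such changes. Simulated results at effect 0.25 (1,500 runs each), for change from baseline:

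| Assumed R² | Power: none | Power: stated rule | Power: all seven |
|---|---|---|---|
| 0.05 | 85.7% | 85.7% | 85.3% |
| 0.10 | 85.4% | 85.3% | 84.9% |
| 0.20 | 85.7% | 85.5% | 85.6% |

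The SE was 0.083 throughout. A five-visit maximum-likelihood fit with unstructured covariance (40 simulated trials, complete data) gave the same interaction estimate at 6 months with no covariates or all seven, SE 0.0826 both ways. With 10% monotone dropout, the largest difference in the estimate was 0.011 SD, and the SEs were 0.0854 and 0.0853.

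**Step 5. Where precision is available.** With outcome SD 1 at each visit, the variance factor is 2(1 − rho) for change from baseline and 1 − rho² with baseline as a covariate. The ratio is (1 − rho²)/[2(1 − rho)] = (1 + rho)/2.

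| Assumed rho | Change | Baseline as covariate | Ratio | Power at 289: change | Power at 289: covariate |
|---|---|---|---|---|---|
| 0.3 | 1.40 | 0.91 | 0.65 | 71.9% | 88.3% |
| 0.5 | 1.00 | 0.75 | 0.75 | 85.2% | 93.4% |
| 0.7 | 0.60 | 0.51 | 0.85 | 97.3% | 98.8% |

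**Step 6. What demographics add after that.** With baseline loneliness already a covariate (rho = 0.5), always including all seven moved simulated power from 93.3% to 93.8% at R² = 0.05, from 93.5% to 94.3% at 0.10, and from 93.1% to 94.7% at 0.20.

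**The case against.** The strongest defence is that the rule does almost nothing in this model. The effect is a Group by Time interaction with baseline among the Time levels, and no covariate-by-time term is stated, so the demographics largely cancel. The covariate list may change, but the answer hardly does. Step 4 bears this out, and it limits the point to unsound specification and an unused source of precision.

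Two stronger readings are tempting and are not supported.

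- A reader might infer that the rule costs several points of power. For a single follow-up contrast it can: at R² = 0.20, simulated power was 84.2% unadjusted, 84.7% under the rule and 91.1% with all seven always included. But the protocol does not plan that contrast, and the documents do not support an R² of that size. Eligibility restricts everyone to age 65 or over, living alone and low income, which narrows some of these variables.
- A reader might infer from Table 1, where a row for covariates is marked at baseline and at the 4-week follow-up, that post-treatment values would be adjusted for. Table 1 has a separate row for socio-demographic variables, marked at baseline only, and the rule concerns demographics that differ at baseline. A mark in a schedule shows collection, not entry into a model.

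The 30% figure is also an upper value under independence at an assumed 5% level; related demographics would lower it. That stands.

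**Conclusion.** The point holds in a limited form. The rule is unsound in principle: it selects on chance imbalance and leaves the covariate set to be settled by the data, with up to about a 30% chance that at least one of seven demographics enters. It does not inflate type I error and has little effect on the planned Group by Time estimate or its SE.

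The larger consequence is what the adjustment plan leaves unused. With baseline loneliness handled as a Time level with free means, the contrast behaves like change from baseline. Using it as a covariate, or constraining baseline means, would multiply the variance by 0.65 to 0.85 for rho between 0.7 and 0.3 taken in reverse order, that is 0.65 at 0.3 and 0.85 at 0.7. At rho = 0.5, power at 289 per arm goes from 85.2% to 93.4%. These figures rest on assumed correlations, equal variances across visits, complete data and a visit-specific contrast; a growth slope across visits would give different numbers.

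**What to change.** 1. Delete the sentence that makes adjustment depend on significant baseline differences, and replace the baseline tests between arms with descriptive tables.
2. Use baseline loneliness in every loneliness model, either as a covariate with only post-baseline visits as outcomes, or by keeping baseline in the outcome vector and constraining its mean to be equal across arms.
3. Name a short list of baseline demographics from the seven, chosen for expected relation to loneliness and kept regardless of observed balance. If baseline stays in the outcome vector, add covariate-by-time terms, since main effects alone largely cancel.
4. Recruitment was complete and follow-up still running at this version, so make the choice without looking at baseline data by arm and before outcome data are analysed.

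The variables are already collected. The cost is a change of wording and a few degrees of freedom.

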#### Methods

In a three-arm randomized controlled trial, older adults in Hong Kong who live alone and under the poverty line, do not have Internet at home, and feel lonely will be randomly assigned to receive one of the three interventions (enrollment goal,  $N = 966$ ). The primary outcomes will be loneliness, social network indicators and perceived social support. Secondary outcomes will be perceived stress, sleep quality, anxiety and depressive symptoms, physical and cognitive health. Underlying mechanisms will be examined with mindfulness, activity happiness/meaningfulness, diurnal cortisol patterns, levels of the salivary C Reactive Protein, and genetic markers (candidate gene, GWAS, biological pathway related SNPs, and polygenic risk scores).

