## Supplement 1. Study Protocol

**Biomarkers.** One third of participants in the sample will be invited to provide saliva samples. After providing detailed guidelines in saliva sample collection, three saliva samples are collected by the participants using Salivette tubes at the participants' homes on 2 consecutive weekdays, three times each day: after waking up, before lunch, and before bedtime, 4 time points (baseline, 4-week, 3-month and 6-month follow-up). Standard instruction procedures and a telephone reminder are provided to participants. The collected Salivette tubes are kept frozen, and the cortisol levels are determined according to the manufacturer's standard using an ELISA kit (Salimetrics, PA, USA). Each participant's diurnal cortisol pattern is identified using four indicators: (1) morning cortisol, (2) evening cortisol, (3) mean cortisol, and (4) the diurnal cortisol slope. Salivary samples are also tested for CRP using the Salivary C-Reactive Protein ELISA kit according to the manufacturer's recommended protocol (Salimetrics, PA, USA).

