**Genotyping.** DNA is collected from saliva samples at baseline, and the Infinium OmniZhongHua-8 v1.3 BeadChip with 887,270 SNPs are used, as this type of chip has been widely used for genotyping in Chinese populations. This type of chip is designed to pay particular attention to alleles found in Chinese populations and is the best choice in terms of study design and cost. It covers common, intermediate, and rare variants found in Chinese populations for genome-wide association studies (GWAS). According to the manufacturer's information, it covers 77% of common variants (minor allele frequency [MAF] > 5%), 73% of intermediate variants (MAF > 2.5%), and 65% of rare variants (MAF > 1%) in Chinese populations at  $r^2 \geq 0.8$ . The assay has exceptionally high data quality in terms of call rates (average > 99%), reproducibility (> 99.9%), and low sample repeat rates, and has high signal-to-noise ratios and low overall noise levels, enabling accurate and reliable calls and copy number analysis. The Sequenom platform is used in the second stage of variant genotyping. The Sequenom system is based on single-base extension (SBE) chemistry and mass spectroscopy, and allows SNPs to be designed for 40-plex assays. If it is necessary to sequence candidate genes, mutation screening is conducted by direct sequencing of exons, intron-exon boundaries, and conserved promoter elements using the ABI 3730XL sequencer in the CGS HKU genotyping core facility. Thus, candidate genes, GWAS, polygenic risk scores, and SNPs from underlying biological pathways are used as genetic dispositions.

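### One 95% bootstrap rule is applied to SNPs as well as to a few behavioural and salivary mediators, with no limit on the number of SNPs, so the rate of false genetic mechanisms is uncontrolled

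*Protocol*

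**What the plan says.** In the Protocol, under Planned Analysis of the Effects of the Intervention, mediation is examined by path analysis with "indirect effect specified and tested with 95% bias-corrected confidence intervals resulting from 1000 bootstraps in Mplus 8". The sentence that follows lists mindfulness, events and CRP, and adds that "the position of candidate genes, polygenic risk scores and SNPs are potential mediators to be tested". The same interval level and number of draws thus apply to a questionnaire score and to a SNP.

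Under Mediators, Genotyping, the Protocol states that "the Infinium OmniZhongHua-8 v1.3 BeadChip with 887,270 SNPs are used" and that "candidate genes, GWAS, polygenic risk scores, and SNPs from underlying biological pathways are used as genetic dispositions". The Methods part of the Abstract also lists GWAS among the genetic markers for underlying mechanisms. On timing, "DNA is collected from saliva samples at baseline"; the Randomization section places allocation after the baseline assessment. On sample size, under Biomarkers, "One third of participants in the sample will be invited to provide saliva samples".

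The Protocol does not state how many SNPs enter the path models, a list of them, an adjusted level or a genome-wide threshold. The second genotyping platform is described as an assay, not as a replication step.

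**The concern.** A 95% interval per variable is a workable rule for a handful of mediators. It stops being one when the number of variables is open-ended and could reach hundreds or more, because some markers will pass by chance. Genetic mechanisms are an announced output of the trial. If the rule is followed on a long set of SNPs, it will return a list of apparent genetic mechanisms whether or not any exist, and a reader could not tell a true list from a chance one.

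A second fault makes this worse. Genotype is inherited and fixed before randomization, so the true path from arm to SNP is zero. Every SNP flagged as a mediator is then a false positive, whatever threshold is used.

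**Working it through.** The Protocol gives no error rate for the mediator tests, so there is no stated figure to reproduce.

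**Inputs from the Protocol.** 95% bias-corrected interval, 1000 draws; 887,270 SNPs on the chip; 966 participants, one third invited for saliva: 966/3 = 322, or about 322/3 = 107 per arm and 214 in a two-arm contrast.

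**Assumptions.** Number of SNPs tested (not stated, so a range); allele frequencies of 0.05 to 0.5; SNP independent of arm.

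**Step 1: flag rate per SNP.** The stated rule was simulated for the product a×b (arm to SNP, SNP to loneliness).

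- No genetic effect, 107 per arm, 4,000 replicates: 0.60% at allele frequency 0.30 and 0.75% at 0.05.
- No genetic effect, a separate run with 10,000 null SNPs per setting: 0.56% at 214 participants in the contrast, 0.57% at 322, 0.54% at 644.
- SNP predicts loneliness but is unrelated to arm: 7.0% at 0.2 SD per SD of genotype with 107 per arm; 5.4% to 7.8% across effects of 0.15 and 0.3 and the three sample sizes.

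The null rate lies well below 5% because both paths must look non-zero by chance. I use 0.6%.

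**Step 2: chance of at least one false declaration**, 1 − (1 − p)^m for m independent tests, for one contrast and one outcome. The last column applies if the SNPs were tested as effect modifiers at 95%, where a check gave about 5% per test.

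| m | mediation, p = 0.006 | effect modification, p = 0.05 |
|---|---|---|
| 10 | 1 − 0.994^10 = 6% | 1 − 0.95^10 = 40% |
| 40 | 21% | 87% |
| 100 | 45% | 99% |
| 500 | 95% | above 99% |

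Each further contrast or outcome adds tests.

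**Step 3: whole chip.** Expected false declarations = 887,270 × 0.006 = 5,324 per contrast and outcome. This expectation does not require independence, so linkage between SNPs does not alter it. For effect modification it would be 887,270 × 0.05 = 44,364.

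**Step 4: can the bootstrap be tightened?** The smallest two-sided tail that 1000 draws resolve is 2/1000 = 0.002. Bonferroni reaches that limit at 0.05/0.002 = 25 tests. For the whole chip the level is 0.05/887,270 = 5.6e-8, far below it.

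**The case against.** The strongest objection concerns reach. The figure of 887,270 is the content of the chip, not a stated number of mediation tests. The analysis section names candidate genes, polygenic scores and SNPs but not GWAS, so the SNPs meant there may be a short candidate or pathway list. This stands. A reader might infer that the plan as written produces false genetic mechanisms almost with certainty; the documents support that only for long lists or a genome-wide scan. At 10 SNPs the chance is about 6%.

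Two further inferences also go too far. One is that the bootstrap rule cannot be tightened at all: up to about 25 tests, 1000 draws just suffice. The other is that the 0.6% rate would apply if genotype were re-entered as an effect modifier: it belongs to the product of two null paths, and an interaction test has about 5%.

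It can also be said that thresholds for exploratory genetics belong in an analysis plan, which may exist. This carries less weight. The Protocol is not silent: it fixes the level, the interval type and the number of draws, and assigns them to SNPs by name. A later plan could add an adjustment, but it would have to change how this rule is read.

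Finally, the stated hypotheses concern loneliness, and the variables are called potential mediators. That limits the consequence, but does not repair the rule.

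**Conclusion.** The point holds in a conditional form. The Protocol applies one per-marker 95% bootstrap rule to SNPs without bounding their number, and so leaves the rate of false genetic mechanisms uncontrolled. How large that rate is depends on a count the Protocol does not give: modest for about ten SNPs, close to even odds at 100, and near certain from several hundred independent tests upwards or on a chip scan. These figures rest on the simulated null rate of about 0.6% and, for the probabilities, on independent tests; SNPs that predict loneliness would be flagged some ten times as often.

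The multiplicity fault is not the only one. Because treatment cannot alter inherited genotype, a stricter threshold alone would still leave a test whose every positive result is a chance finding. The treatment comparisons on primary and secondary outcomes are not affected. The change should be made because genetic mechanisms are a declared output.

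**What to change.** Amend Planned Analysis of the Effects of the Intervention as follows.

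1. Keep the bootstrap intervals for indirect effects for mindfulness, events and the salivary markers only.
2. State that inherited genotype is not tested as a mediator. Test it as an effect modifier, through a genotype × group interaction.
3. Name the polygenic score to be tested, state the outcomes and arm contrasts, and adjust across them.
4. Fix the list of candidate-gene and pathway SNPs before outcome data are analysed, and apply Bonferroni or a 5% false discovery rate over all tests on that list, counting contrasts and outcomes.
5. Judge any genome-wide scan at 0.05/887,270 = 5.6e-8, using model-based p-values, because 1000 draws cannot resolve p below about 0.002.

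This is a change of wording and needs no new data or participants. The cost is that fewer SNPs will be reportable as significant.
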